#### Acupuncture treatment group

Sterile, disposable, stainless steel needles of various lengths and diameters (Huatuo Medical Instruments Co. Ltd., Suzhou, China; 0.3 mm × 25 mm/0.3 mm × 40 mm) will be used in the intervention group. All acupoints will be punctured by filiform needles when patients are in a comfortable sitting position. The depth of these needles will be adjusted to the standard permissible layers of each acupoint. Then an even reinforcing-reducing technique, which means lifting, thrusting, twisting, and rotating the needles moderately, will be performed on the needles until achieving the *de-qi* sensation. The needles will be retained for 30 min in each session and manipulated every 10 min with intermittent stimulation to maintain the *de-qi* sensation. The manipulation of each acupoint will last for 10 s.

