### Blinding

All the participants, outcome assessors, and statisticians will be blinded to treatment allocation during the whole study. Due to the characteristics of the acupuncture clinical trial, it is not possible to blind the acupuncturists to treatment allocation in this trial. Therefore, they will not take part in the assessment procedure. Different treatment groups will receive treatment in different rooms to blind the participants to their treatment allocation. We will indirectly assess the success of blinding by testing credibility after all the treatment sessions [30], and participants will be asked to guess what kind of acupuncture treatment they have received.

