### Interventions

In this trial, treatment strategies were developed by consensus with experienced acupuncture practitioners and dermatologists. There are two groups: active acupuncture group and sham acupuncture (superficial non-acupoint acupuncture) group. The location and manipulation of fixed acupoints and non-acupoints are shown in Table 1. Participants in both groups will receive 10 sessions of acupuncture over 2 weeks. Each session will be administered once a day for 5 days consecutively followed by a 2-day rest interval. All acupuncture treatment sessions will be performed by two acupuncturists who are registered Chinese Medicine Practitioners in China and have at least 3 years’ clinical experience in acupuncture practice. Acupuncturists will also receive training before this trial. Contents of the training classes cover the locating of acupoints, needle manipulation skills, and communication skills. The acupuncturists can be admitted to participate in the trial when they can pass the trial training examination.

**Table 1 Tab1:** Locations and manipulations of the acupuncture points selected in this study

Group	Acupoints	Location	Manipulation
Acupoint	Baihui (GV20)	In the head, the front of the forehead is straight up to 5 cun	Subcutaneous insertion to a depth of 0.5–0.8 cun (12.5–20 mm) with manipulation for the *de-qi*
	Shenting (GV24)	In the head, the front of the forehead is straight up to 0.5 cun	Subcutaneous insertion to a depth of 0.5–0.8 cun (12.5–20 mm) with manipulation for the *de-qi*
	Quchi (LI11)	At the elbow, the midpoint of the lateral end of the elbow transverse line and the upper tibia	Puncture perpendicularly to a depth of 1–1.5 cun with manipulation for the *de-qi*
	Zhongwan (CV12)	In the upper abdomen, 4 cun above the umbilicus, the front midline	Puncture perpendicularly to a depth of 1–1.5 cun with manipulation for the *de-qi*
	Tianshu (ST25)	In the abdomen, parallel to the umbilicus, 2 cun in front of the front midline	Puncture perpendicularly to a depth of 1–1.5 cun with manipulation for the *de-qi*
	Xuehai (SP10)	In the anterior region of the femoral, 2 cun above the medial end of the patella and the protuberance of the vastus medialis	Puncture perpendicularly to a depth of 1–1.5 cun with manipulation for the *de-qi*

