#### Sham-acupuncture treatment group

Participants assigned randomly to this group will be given superficial non-acupoint acupuncture 10 times over 2 weeks. The same type of acupuncture needle will be inserted perpendicular to the skin at a depth of 1.0–3.0 mm and the needles will be retained for 30 min without any manipulation to avoid the deqi sensation as much as possible. The number of acupuncture points, duration, and frequency of the sessions will be the same as those for the acupuncture treatment group, and the same practitioner will conduct the intervention.

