The chosen primary outcome is change in the symptom of wheals and angioedema as obtained from the 7-day UAS. Multiple guidelines [1, 15] and a consensus statement [3, 16] recommend the UAS as the main outcome, and the UAS had been widely used as an outcome measure in CU studies. At the same time, assessment of the severity of CU has mainly depended on patient-reported outcomes. The VAS score for itching intensity can directly assess the variations in the severity of subjective symptoms. The available data indicate that urticaria markedly affects both objective functioning and subjective well-being [56–58]. In this trial, we use the DLQI to evaluate quality of life in patients with CU before and after acupuncture treatment. The DLQI is extensively used in evaluating quality of life in skin disease. It is safe and convenient, and also various different language versions of the DLQI are more readily available than the CU Quality of Life Questionnaire (CU-Q2oL) and the Angioedema Quality of Life Questionnaire (AE-QoL). We have obtained the authorization of the Chinese version of DLQI from Finlay [36]. We will also test for correlation between the symptoms of CU and psychiatric disorders by evaluating the HAMD and HAMA in this study. The Humoral immunity index and measurement of serum total IgE will be experimentally assessed to evaluate possible correlation between immunity and the mechanism of the effects of acupuncture on CU.

This trial has its limitations. First of all, this clinical trial will include a small population of participants and will not primarily aim to perform hypothesis testing. For this reason, the results of this study cannot be generalized as basic data for assessing the effect and safety of acupuncture for treatment of CU. Furthermore, because the control group will receive minimal acupuncture, we cannot ignore the possibility of physiological activation caused by needle penetration. The effect of acupuncture will need to be carefully interpreted because the acupuncture points, needling depth, and *de-qi* will be the only differences assessed between groups.

To summarize, this study is funded by the National Key Research and Development Program of the China-Key Project. The study protocol describes the first randomized, patient-blinded and assessor-blinded, sham-controlled trial. The findings of the study will provide feasibility data and basic information about the effect and safety of acupuncture for a future, full-scale RCT in CU.

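### Separate rooms do not hide a participant's own needles, so a seated participant who knows real needling could recognise the sham by sight

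*Protocol article*

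**What the plan says.** The protocol article claims, under Blinding, that participants do not know their allocation at any time in the study. Apart from the sham itself, the measure it names is this: "Different treatment groups will receive treatment in different rooms to blind the participants to their treatment allocation". It adds a credibility test after the last session and asks participants which treatment they think they had.

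On posture and needles, the section on the acupuncture arm says: "All acupoints will be punctured by filiform needles when patients are in a comfortable sitting position". The needles are "0.3 mm × 25 mm/0.3 mm × 40 mm". They stay in for 30 minutes and are worked again every 10 minutes. The sham section says: "The same type of acupuncture needle will be inserted perpendicular to the skin at a depth of 1.0–3.0 mm". Those needles also stay in for 30 minutes, but nobody manipulates them. The sham section gives no posture. The Discussion says that "the acupuncture points, needling depth, and *de-qi* will be the only differences assessed between groups", which implies that sham participants sit as well.

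In Table 1, the limb and abdominal acupoints carry the instruction "Puncture perpendicularly to a depth of" 1 to 1.5 cun (1.0 cun at SP6), against 1 to 3 mm at every sham point.

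Wheals and itching, the two parts of the UAS, are entered by participants in a daily diary (Setting of the study). Participants also mark the itch VAS themselves, and the DLQI is a questionnaire.

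**The concern.** The primary outcome and two main secondary outcomes are supplied by the participant. Independent assessors cannot protect a score that comes from someone who has worked out their allocation, so these outcomes depend on the participant blind.

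The named measure deals with one route to unblinding, which is comparison with participants in the other arm. It leaves a second route open: what participants see on their own body over ten half-hour sessions. Long needles standing almost wholly outside the skin and never touched look different from needles that are deeply seated and worked at intervals. The Abstract says acupuncture is widely used for this disease in China, and previous acupuncture is not an exclusion criterion, so some participants may know the difference.

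If sham participants recognise the sham and rate their symptoms accordingly, the comparison shifts in favour of real acupuncture. The pilot is meant to supply starting figures for a full-scale trial, so both the weak point in the masking and a distorted effect estimate could be carried forward.

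**Working it through.** **Inputs from the article**
- Conversion (Table 1): 0.5–0.8 cun is given as 12.5–20 mm. 12.5 / 0.5 = 25 and 20 / 0.8 = 25, so the table's own figures agree on 1 cun = 25 mm.
- Needle lengths: 25 mm and 40 mm, not assigned to individual points. The sham uses the same type.
- Sites: eight per arm. The real set has two on the head (GV20, GV24) and six elsewhere (LI11 elbow, CV12 and ST25 abdomen, SP10 thigh, ST36 and SP6 lower leg). ST36 and SP6 count as real points because they are needled deeply for *de-qi* and because the number of points is said to be equal in both arms. The sham set has two on the head and six on the forearm, abdomen (two), thigh and lower leg (two).

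**Assumptions**: the stated needle length is the shaft without the handle, and depth is measured along the shaft.

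**Formula**: exposed shaft = needle length − insertion depth, with a minimum of 0.

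**Six body sites.** Real depth is 1 × 25 = 25 mm to 1.5 × 25 = 37.5 mm (SP6: 25 mm). Sham depth is 1–3 mm.

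| Needle | Real arm | Sham arm |
|---|---|---|
| 25 mm | 0 mm | 25 − 3 = 22 to 25 − 1 = 24 mm |
| 40 mm | 40 − 37.5 = 2.5 to 40 − 25 = 15 mm | 40 − 3 = 37 to 40 − 1 = 39 mm |

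Across both needle lengths the range is 0–15 mm real and 22–39 mm sham. The smallest gap for any pairing is 22 − 15 = 7 mm. With the same needle length in both arms it is 22 mm (37 − 15, or 22 − 0).

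**Sensitivity to the cun.** The longest real exposure is 40 − c, where c is the length of 1 cun in mm. It reaches the sham minimum of 22 mm only at c = 18. For c from 20 to 33.3 there is no overlap: the longest real exposure runs from 20 mm down to 6.7 mm.

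**Two head sites.** Real depth is 12.5–20 mm. A 25 mm needle leaves 5–12.5 mm, again below the sham range. A 40 mm needle would leave 20–27.5 mm, which overlaps the sham's 22–24 mm. Participants cannot see these sites.

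**Second visible cue.** Over 30 minutes, real needles are worked again at 10-minute intervals, for 10 seconds per point. Sham needles are left alone.

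**What each stated measure covers**
- Separate rooms: prevent comparison between participants; do not cover one's own needles.
- Same needle type, number of points, duration, frequency and practitioner: make the sham resemble the real procedure; do not equalise depth or manipulation.
- Credibility test and treatment guess: detect unblinding after the last session; do not prevent it.

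**The case against.** The strongest reply is that this is a gap in a condensed article. It does not say that participants watch the needles, it is silent on drapes, screens and clothing, and the operating procedures it mentions are not shown. That stands as far as it goes: a barrier may already be in use. But the article is not silent on masking. It names a measure, and that measure does not reach this cue.

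Second, participants see only their own needles. The difference between arms is not itself what unmasks anyone; a long exposed shaft means something only to a person who knows how real needling looks. This stands. The article gives no data on participants' acupuncture experience, so recognition is possible but not shown.

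Third, visibility is inferred from a sitting posture and the location of the points. Sight lines are not described, some lower-leg and abdominal sites may be hard to see, and sitting is written only for the real arm. This stands too.

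Fourth, *de-qi* and manipulation can be felt, so blocking the view removes only part of the information. The Discussion already urges careful interpretation on that account. True, but a remaining felt cue is no reason to leave a visible one in place.

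Finally, this is a pilot not meant for hypothesis testing, and it plans to check blinding. That lowers the stakes and deserves credit, but the check comes when treatment is over.

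**Conclusion.** The point holds as a cheap improvement. The article's named blinding measure leaves a visible cue open at six of eight sites per arm: 0–15 mm of exposed shaft with real needling against 22–39 mm with sham, plus manipulation in one arm only. This rests on the Table 1 conversion, the two stated needle lengths, and sham participants also being seated. Recognition would tend to favour real acupuncture in the UAS, VAS and DLQI.

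A reader might infer more, and the documents do not support it:
- That participants do see their needles, or that blinding will fail. Neither follows from posture and anatomy.
- That exposed length differs at every site. This is certain only at the six body sites, because needle length per point is not given.
- That a UAS bias can be quoted. Any figure is an assumed share recognising the sham times an assumed shift in score. For example, 10–50% and 1–5 points give 0.10 × 1 = 0.1 to 0.50 × 5 = 2.5 points, a 25-fold span set wholly by the assumptions.

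**What to change.** At every session and in both arms, block the participant's view of the needled sites in the same way (drape, screen or eye mask) from before insertion until after removal. State this under Blinding and in both intervention sections, and say there that posture is the same in both arms if it is. Leave the needling itself unchanged. If a barrier is already used, one sentence saying so settles the point. Keep the credibility test and treatment guess as the check.

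The cost is the material, a line in the procedures and slight inconvenience to participants; no extra staff are needed. Felt cues would remain. The trial started on 16 July 2018, so only participants still to be treated, and the full-scale trial, would benefit.

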#### Sham-acupuncture treatment group

Participants assigned randomly to this group will be given superficial non-acupoint acupuncture 10 times over 2 weeks. The same type of acupuncture needle will be inserted perpendicular to the skin at a depth of 1.0–3.0 mm and the needles will be retained for 30 min without any manipulation to avoid the deqi sensation as much as possible. The number of acupuncture points, duration, and frequency of the sessions will be the same as those for the acupuncture treatment group, and the same practitioner will conduct the intervention.

### Outcome measurements

The time schedule of enrolment, interventions, assessments, and visits of participants is shown in Fig. 2. The following outcomes will be assessed by independent assessors.

**Fig. 2 Fig2:**
[figure not shown]
Timetable of treatment and outcome collection

#### Primary outcome

The primary outcome measurement is the urticaria activity score (UAS) [1, 31]. The UAS, which is used to make daily assessments for 1 week, combines daily wheal numbers (0 = none, 1 = < 20 wheals/24 h, 2 = 20–50 wheals/24 h, and 3= > 50 wheals/24 h or large confluent areas of wheals) and pruritus intensity (0 = none, 1 = present but not annoying or troublesome, 2 = troublesome but does not interfere with normal daily activity or sleep, and 3 = severe pruritus, which is sufficiently troublesome to interfere with normal daily activity or sleep). It has a total score of 42 points for 1 week. The primary outcome measurement will be assessed at baseline and at 1, 2, 3, and 4 weeks after randomization.

#### Secondary outcome

##### Visual analogue scale (VAS) score of itching intensity per 1 week

The VAS is widely used for the assessment of variations in the severity of subjective symptoms. Participants mark their symptom severity on a 100-mm straight line whereby the extreme left end indicates “absence of symptoms” and the extreme right end indicates “unbearably severe symptoms” [32, 33]. The outcome measurement will be assessed at baseline and at 1, 2, 3, and 4 weeks after randomization.

##### Dermatology Life Quality Index (DLQI)

The DLQI is a compact questionnaire, which is applicable to individuals with any skin disease. It measures the influence of CU on the participant’s life over the previous 7 days. It consists of 10 questions with Likert-type responses and its score ranges from 0 to 30. Higher scores imply greater influence on health-related quality of life [34–36]. The outcome measurement will be assessed at baseline and at 1, 2, 3, and 4 weeks after randomization.

##### Hamilton Depression Scale (HAMD)

The HAMD comprises 17 items, which have been rated on a 3-point or 5-point scale. The HAMD total score ranges from 0 to 52. Clinicians can assess the intensity and frequency of depressive symptoms [37]. Higher scores imply greater depression (severe depression, score ≥ 24; presence of depression, score ≥ 17; possible depression, score ≥ 7; and no depression, score < 7). The outcome measurement will be assessed at baseline and at 2 weeks after randomization.

##### Hamilton Anxiety Scale (HAMA)

The HAMA is a 14-item clinical interview measure of somatic and psychic anxiety symptoms that have been rated on a 4-point scale [38]. The HAMA total score ranges from 0 to 56. Higher scores are positively correlated with higher levels of anxiety (severe anxiety, score ≥ 24; obvious anxiety, score ≥21, some degree of anxiety, score ≥ 14; possible anxiety, score ≥ 7; and no anxiety, score < 7). The outcome measurement will be assessed at baseline and at 2 weeks after randomization.

##### Humoral immunity index and measurement of serum total IgE

Although the clinical diagnosis of CU is straightforward, the etiology and pathogenesis of CU remain obscure. There is some evidence [39, 40] that the pathogenesis of CU is closely related to serum humoral immunity and serum total IgE. In this study, we will investigate the levels of serum immunoglobulins (IgG, IgA, and IgM), the complement components (C3 and C4), and serum total IgE before and after treatment in the two groups.

These laboratory tests will be measured using an enzyme-linked immunosorbent assay (ELISA). About 4 ml of whole blood will be collected from participants at two time points - at baseline and at 2 weeks after the completion of acupuncture treatment. Changes in various biomarker levels from baseline to 2 weeks will be examined in each of the treatment groups. Between-group differences will be analyzed to observe potential associations with the effect of acupuncture. These related tests will be conducted by the clinical laboratory of the Affiliated Hospital of Chengdu University of Traditional Chinese Medicine.

##### Adverse events

The participants will be requested to voluntarily report information about adverse events such as pallor, sweating or dizziness, fainting during acupuncture treatment, bleeding, local hematoma, unbearable prickling, and continuous severe pain more than 1 h after acupuncture. The acupuncturists will be requested to report adverse events related to the acupuncture such as sticking of the needle, broken needles, bent needles, and needles being retained after treatment. All adverse events will be fully recorded on the adverse event pages of the case report forms (CRFs). The researcher will confirm the occurrence of adverse events and record all details such as the date of occurrence, time, degree, measurement related to the treatment, and causal relationship with the treatment. Emergency medical assistance will be sought if any serious adverse effect occurs, and all details will be noted. The outcome measurement will be assessed at 1 and 2 weeks after randomization.

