**Methods/design:**

This randomized, sham-controlled, participant-blinded and assessor-blinded pilot trial is underway in China. A total of 60 participants with CU will be randomly assigned to two groups in a 1:1 ratio: one treated with real acupuncture and the other with sham acupuncture, for 10 sessions over 2 weeks. The experimental group will receive acupuncture on a fixed prescription of acupoints, whereas the control group will receive sham acupuncture, namely minimal acupuncture on non-acupuncture points. The primary outcome will be the urticaria activity score (UAS). The secondary outcomes will include a visual analogue scale (VAS) score for itching intensity, the Dermatology Life Quality Index (DLQI), the Hamilton Depression Scale (HAMD), the Hamilton Anxiety Scale (HAMA), the humoral immunity index, serum total IgE, and adverse events. The UAS, VAS for itching and the DLQI will be conducted at baseline and at 1, 2, 3, and 4 weeks after randomization. The HAMD, HAMA, humoral immunity index, and serum total IgE will be assessed at baseline and at 2 weeks after randomization. Adverse events will be summarized at 1 week and 2 weeks after randomization.

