### Statistical analysis

All data will be presented as means and standard deviations or number (percentage), and all analyses will be based on the intention-to-treat principle. For the description of baseline characteristics, the mean with standard deviation or range with the minimum and maximum values for continuous data and frequency with percentage for dichotomous data will be reported. Homogeneity between the two groups in terms of baseline characteristics will be tested using the two-sample *t* test for continuous data and the chi square (χ2) test for dichotomous data. Analysis of covariance (ANCOVA) or logistic regression will be used for analysis and adjustment of baseline characteristic that differ significantly between the two groups.

The primary outcome of this study is the cumulative UAS in each group. After a normality test, the total score will be compared using the independent *t* test (parametric) or the Mann-Whitney U test (non-parametric) according to the normality of the data. In secondary outcome analysis, the VAS score for itching intensity and the DLQI will be used to analyze the difference, and differences between groups in mean change between baseline and measurements made at 1, 2, 3, and 4 weeks will be analyzed by repeated measures two-factor analysis. The HAMA, HAMD, humoral immunity index, and serum total IgE measurement will be compared using the independent *t* test (parametric) or the Mann-Whitney U test (non-parametric) according to the normality of the data. The χ2 test or logistic regression will be used to analyze dichotomous outcomes. Adverse events will be compared between groups using the χ2 test or Fisher’s exact test. Missing values will be replaced using the method of last observation carried forward. If the participant dropout rate is > 20%, sensitivity analysis will be conducted with the data included.

All statistical tests will be two-sided, and *p* < 0.05 will be considered statistically significant. The statistical software of SPSS (SPSS, SPSS Inc., Chicago, USA) version 21.0 will be used for the analysis.

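### Adverse-event ascertainment is only partly blinded: acupuncturists who know the arm report acupuncture-related events, and the person judging causality is not said to be blinded

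*Protocol article*

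**What the plan says.** The protocol article's abstract (Methods/design) names the secondary outcomes, ending with "the humoral immunity index, serum total IgE, and adverse events". The Outcome measurements section opens the list of outcomes with "The following outcomes will be assessed by independent assessors". The Blinding section states "All the participants, outcome assessors, and statisticians will be blinded to treatment allocation during the whole study", and of the practitioners it says that "it is not possible to blind the acupuncturists to treatment allocation in this trial. Therefore, they will not take part in the assessment procedure".

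The Adverse events section then describes two sources. For clinical symptoms, "The participants will be requested to voluntarily report information about adverse events such as pallor, sweating or dizziness", with fainting, bleeding, hematoma and pain among the further examples. For the operator's side, "The acupuncturists will be requested to report adverse events related to the acupuncture such as sticking of the needle", followed by broken, bent and left-behind needles. The section adds that every adverse event is to be entered on the case report form. A researcher confirms that each event occurred and records its details, including severity and causal relationship. Nothing is said about whether that researcher knows the allocation.

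The Data collecting and monitoring section has designated outcome assessors enter data on the paper forms. The Statistical analysis section says: "Adverse events will be compared between groups using the χ2 test or Fisher’s exact test".

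**The concern.** A reader of the Blinding and Outcome measurements sections would take all outcomes, safety included, to be ascertained by people who do not know the arm. For adverse events this holds only in part.

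Two steps are exposed. The first is notification. The acupuncturists are asked for events related to the acupuncture, and deciding what is related is a judgement. They make it knowing whether the participant had deep, manipulated needling or insertion to 1–3 mm without manipulation. The second is confirmation and attribution, where the blinding of the responsible researcher is left open.

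At stake is how a between-group difference in adverse events, or the absence of one, is read. Safety is a stated aim of the pilot, and its procedures are meant to inform a full-scale trial. A weakness in safety ascertainment would be carried forward if it is not corrected here.

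**Working it through.** No calculation decides this point. The document gives no adverse-event rate and no reporting rate, so there is no figure to reproduce. The check follows an event through the protocol article and asks at each step who acts and whether that person is blinded.

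| Step | Who acts | Blinded? | Section |
|---|---|---|---|
| Symptom noticed and volunteered | Participant | Yes | Adverse events; Blinding |
| Needle or session event noticed and reported, if related to the acupuncture | Acupuncturist | No | Adverse events; Blinding |
| Occurrence confirmed, severity and causality recorded | Researcher | Not stated | Adverse events |
| Data entered on the paper form | Designated outcome assessor | Yes | Data collecting and monitoring; Blinding |
| Groups compared | Statistician | Yes | Statistical analysis; Blinding |

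Reading across the rows:

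1. *Is the outcome covered by the general statement on assessment?* Yes. The sentence "The following outcomes will be assessed by independent assessors" stands above all the outcome subsections, and adverse events are one of them.

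2. *Do the acupuncturists contribute to this outcome?* Yes, as the second of two sources. The Blinding section says of them: "Therefore, they will not take part in the assessment procedure". Notifying an event need not count as assessing it. Selecting which events are related comes closer, because the Adverse events section itself treats the causal relationship as something the researcher is to determine.

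3. *Does the promise to record every adverse event close the gap?* Not fully. It can cover only events that reach the form. Consider an event that the acupuncturist observes and judges unrelated, and that the participant does not volunteer. Neither of the two described routes carries it to the form.

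4. *Does form completion by outcome assessors close the gap?* In part. It puts data entry in blinded hands. It does not make those assessors the people who confirm and attribute adverse events, a task given to a researcher whose blinding is not described.

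5. *Does the reporting rule differ by arm?* No. Sources, rule, forms and assessment times (1 and 2 weeks) are the same in both arms, and the Sham-acupuncture treatment group section has the same practitioner deliver the treatment. The risk is that one rule may be applied differently by someone who knows the arm.

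**The case against.** The strongest reply is that reporting is not assessing. On that reading the acupuncturist notifies, a separate researcher confirms and attributes, blinded assessors fill in the forms, and the sections fit together. The relatedness phrase would then merely name a class of needle-handling events, as opposed to the symptoms that participants report. A broken or bent needle needs little causal judgement, and the operator is the person best placed to see it. Adverse events are also a secondary outcome in a pilot of 60 that disclaims hypothesis testing, and the article openly says that the acupuncturists are unblinded.

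Much of this stands. An operator source is reasonable, the listed examples leave little room for judgement, and the pilot setting limits the weight of the point. It does not settle two things: the wording can be read as a relatedness restriction applied by someone who knows the arm, and the blinding of the person who judges causality is unstated.

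A reader might also infer more than the text supports:

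- *That the safety comparison is not blinded at all.* Blinded participants report the clinical symptoms, and outcome assessors complete the forms.
- *That only acupuncture-related events are collected.* The relatedness wording applies to the acupuncturists' source alone, its examples are illustrative, and all adverse events are to be recorded.
- *That the arms are not compared like for like.* The same rule applies in both. If deeper, manipulated needling produces more needle events, that is a true safety difference between the interventions.
- *That reporting bias of a given size can be expected.* No reporting rates are given, and any chosen pair would be invented.

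**Conclusion.** The point holds in a limited form. Adverse-event ascertainment is partly unblinded, whereas the Blinding and Outcome measurements sections suggest that it is wholly blinded and independent. One type of event has no described route to the record, and the blinding of the causality judgement is left open.

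This rests on reading the Outcome measurements sentence as covering adverse events, which its position supports, and on reading the relatedness phrase as a possible restriction and not merely a label. On the milder reading of that phrase, the unblinded source and the unstated blinding of the researcher remain.

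The size of any distortion cannot be derived from the document, and its direction is not established. The primary outcome is not affected. Severity is minor: a cheap improvement, not a flaw that undermines the trial.

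**What to change.** In the Adverse events section, have the acupuncturists complete the same fixed yes/no list of observed events after every session in both arms, whether or not they think an event is related to treatment. State that an outcome assessor blinded to allocation confirms, grades and attributes the events.

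In the Blinding and Outcome measurements sections, add that events observed during sessions come from an unblinded source.

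In the Statistical analysis section, keep all events in the between-group comparison, and also tabulate needle-handling events and participant-reported symptoms separately so that readers can see which source drives any difference. Needle-handling events should not be removed from the comparison, because that would take procedure-related harms out of the formal safety test.

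The cost is a short form per session: 60 participants × 10 sessions = 600 forms at most, plus a few sentences of text. The sample size and the planned tests do not change.
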